### Theoretical framework guiding research

Protection Motivation Theory is the theoretical framework guiding this research. This theory has been used to identify the predictors of a range of health behaviors, including uptake of whole genome screening [33, 34]. The theory was developed to address the cognitive processes of individuals that mediate the effect of persuasive communications on behavioral change, through the identification of two independent appraisal processes: threat and coping appraisals. The theory proposes that threat appraisals are based on the individual’s perception of their vulnerability towards, and severity of the undesirable health outcome. Their coping appraisal is centered on the perceived costs of their adaptive response: response efficacy and their own self-efficacy towards partaking in the behavior (Fig. 1).

**Fig. 1 Fig1:**
[figure not shown]
Protection Motivation Framework

### Study design

Assessing a woman’s breast cancer risk by profiling common risk variants represents a novel approach in clinical genetics. The PRS results referred to in the protocol are research results obtained from the ViP study and will only be available to the 400 women invited to participate in this psychosocial study.

This is a prospective study which is being conducted across FCCs in two Australian states (Victoria and Tasmania). The study has been approved by the Peter MacCallum Cancer Centre Ethics Committee (HREC/16/PMCC/2) and the Tasmanian Health and Medical Human Research Ethics Committee (H0016395).

The primary psychological outcome measurement is breast cancer anxiety as assessed by the Impact Event Scale (IES). The secondary psychological and behavioral outcomes are: i) general anxiety and depression, ii) test-related distress, positive experiences and uncertainty, iii) concordance with screening guidelines, iv) uptake of preventative strategies, and v) level of decisional regret. The method of determining the PRS has been described elsewhere [9].

Data will be collected through self-reported questionnaires. Over the course of the study, participants will complete up to three questionnaires. Women who choose to receive their PRS result will complete three questionnaires: at baseline (prior to attending the FCC), two weeks after receiving their PRS result, and 12 months after receiving their result. Women who choose not to receive their result will complete two questionnaires: at baseline and 12 months after enrolment in the study (Fig. 2).

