## Methods/design

### Study objectives and hypotheses

The study will invite 400 female participants from the ViP study (including a mixture of index cases and family members) to receive their personal PRS results and will examine the following aims and hypotheses:

**Aim 1.** To determine the interest in polygenic risk assessment and investigate the determinants of accepting this invitation to receive results, i.e. uptake of this offer and factors associated with uptake.

Hypothesis 1a) Compared to women who decline their results (‘decliners’), women who receive their results (‘receivers’) will:i.have higher baseline breast cancer anxiety (primary outcome variable), a need to avoid uncertainty, and they will be more likely to have daughters;ii.be more likely to comply with breast cancer screening guidelines 12 months after receiving their results.

**Aim 2.** Assess the short-(2 weeks) and long-term (12 months) psychological and behavioral outcomes, including compliance with recommended screening and preventative strategies, of ‘receivers’ and ‘decliners’.

Hypothesis 2a) Receivers with a high PRS result will:i.have increased breast cancer anxiety compared to baseline in the short-term (2 weeks after receiving results), but breast cancer anxiety will return to baseline levels in the long-term (12 months after receiving results); and.ii.be more likely to report having implemented risk-reducing strategies 12 months after receiving their results when compared to receivers with a low PRS.

Hypothesis 2b) Unaffected women receiving a low PRS will have decreased breast cancer anxiety 2 weeks after receiving results, which will be sustained at 12 months, compared to affected women who receive a low PRS.

Hypothesis 2c) Affected women who receive a high PRS result will exhibit larger increases in breast cancer anxiety from baseline in the short-term (2 weeks after receiving results), compared to unaffected women who receive a high PRS.

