#### Measures

Women will complete the three self-administered questionnaires over a 12-month period (see Additional file 1). A summary of the measures included at each time point is shown in Table 1.

**Table 1 Tab1:** Measures selected for study and corresponding questionnaires

Measure	Q1 Baseline	Q2 Receivers	Q3 Receivers	Q3 Decliners
Predictor Variables				
1. Demographic characteristics	√			
2. Protection motivation	√			
3. Perceived severity of breast cancer	√			
4. Response efficacy	√			
5. Response cost	√			
6. Self-efficacy	√			
7. Uncertainty avoidance	√			
Confounding Variable				
8. Stressful life events	√		√	√
Predictor and Outcome Variables				
9. Perceived breast cancer risk	√	√	√	
10. Knowledge of familial breast cancer and polygenic risk	√	√	√	
11. Breast cancer anxiety	√	√	√	√
Outcome Variables				
12. General anxiety and depression	√	√	√	√
13. Concordance with screening guidelines	√		√	√
14. Intention to take up and actual uptake of preventative strategies	√	√	√	√
15. Regret over testing decision		√	√	√
16. Recall and interpretation of results		√	√	
17. Test-related distress, positive experiences and uncertainty		√	√	
18. Reasons for declining results				√

Clinical data available through the ViP study includes: number of affected first- and second-degree relatives, including number deceased due to breast cancer, personal history of breast cancer, and for affected women, time since diagnosis.

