#### Outcome variables

12.
*General anxiety and depression:* will be assessed using the Hospital Anxiety and Depression Scale (HADS). The 14-item HADS is a widely used measure of emotional disturbance and has two subscales measuring general anxiety and depression [40]. Each question has four possible responses, with responses scored on a scale from 0 to 3. A total scale score is obtained by summing each item (range 0 to 42) with a higher score indicating more general anxiety and depression.13.
*Concordance with screening guidelines* – six items have been developed in concordance with national guidelines for mammography and clinical breast examination [41] screening using the approach used in a previous study [42]. Participants will be categorized in terms of their concordance to the current screening guidelines.14.
*Intention to take up and actual uptake of preventative strategies –* 15 items have been developed to assess intention and uptake of preventative strategies, including risk-reducing surgery (bilateral mastectomy), medication (i.e. tamoxifen and raloxifen), and lifestyle factors (i.e. alcohol consumption, and exercise).15.
*Regret over testing decision* – will be assessed using the five-item Decision Regret Scale, which correlates with decisional conflict and quality of life [43].16.
*Recall and interpretation of testing results* – three items have been developed to assess recall and understanding of testing results.17.
*Test-related distress, positive experiences and uncertainty –* this measure includes 19 items from a validated questionnaire, the Multidimensional Impact of Risk Assessment Scale [44], assessing distress (six items), positive experiences (four items), and uncertainty (nine items) about genetic testing. Response options range from ‘never’ (0) to ‘often’ (5) with higher scores indicating higher psychological distress.18.
*Reasons for declining results* – will be assessed with 15 items used in a previous study [18]. Women will be asked to indicate the extent to which possible reasons for declining to receive results apply to them.

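### The last questionnaire is timed from disclosure for receivers but from enrolment for decliners, so the planned receiver-versus-decliner comparison has no common time point and may favour receivers if the items accumulate over time

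*Protocol article*

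**What the plan says.** Study design sets two schedules. Receivers are assessed "at baseline (prior to attending the FCC), two weeks after receiving their PRS result, and 12 months after receiving their result". For decliners: "Women who choose not to receive their result will complete two questionnaires: at baseline and 12 months after enrolment in the study". Disclosure is in person, at an appointment with a genetic health professional (Genetic counseling consultation and disclosure of results).

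Hypothesis 1a(ii) predicts that receivers, compared with decliners, will "be more likely to comply with breast cancer screening guidelines 12 months after receiving their results". Aim 2 also covers screening and preventive behaviour in both groups, and Statistical analyses assigns regressions to the receiver-versus-decliner comparison. Table 1 collects screening concordance and preventive uptake from both groups at the final questionnaire.

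Measures describes the overall duration differently: "Women will complete the three self-administered questionnaires over a 12-month period". The Methods paragraph of the Abstract likewise gives one 12-month span.

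On scoring, Outcome variables says of screening: "Participants will be categorized in terms of their concordance to the current screening guidelines". Of prevention it says: "15 items have been developed to assess intention and uptake of preventative strategies", and these strategies include risk-reducing surgery. The article text gives no recall window for either. The questionnaires are in Additional file 1, which is not shown.

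**The concern.** A receiver's clock for the final questionnaire starts at disclosure, but her baseline comes earlier, before the appointment. Her baseline-to-final window is therefore 12 months plus the wait. A decliner's is about 12 months, taking enrolment and baseline as close together. The difference arises from the schedule itself, even if every woman attends as planned.

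Three things follow:

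- Hypothesis 1a(ii) is set at a time point defined by an event that decliners never have.
- The single 12-month period cannot hold for a receiver who waits at all.
- Any outcome that accumulates with time is compared over unequal windows, and the extra time always falls to receivers, the group that 1a(ii) predicts will do better. A higher proportion among receivers could then partly reflect more time rather than an effect of the result.

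**Working it through.** **The plan's own figures.** Sample size and power gives 400 recruited, about 20% lost, and 320 completers made up of 215 receivers and 105 decliners. Check: 400 × 0.8 = 320 and 215 + 105 = 320. These reproduce. No stated figure rests on the timing of the final questionnaire.

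**The two clocks.** Let w be the wait in months from baseline to disclosure.

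- Receiver, baseline to final questionnaire: 12 + w.
- Decliner: 12.
- Difference: w, which the article does not state.

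**Case A: items use a fixed look-back of equal length in both groups.** Under a constant rate of screening, extra calendar time before the look-back adds no opportunity. The artificial difference is 0, and the chance of falsely favouring receivers stays at 2.5% (the upper tail of a two-sided 5% test).

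**Case B: items count events since baseline.** Assume a constant monthly rate and no true group effect, and let p be the proportion of decliners with the event by 12 months. Then

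receivers' proportion q = 1 − (1 − p)^((12 + w)/12).

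With p = 0.50 (assumed):

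- w = 1: q = 0.528, difference +2.8 points
- w = 2: q = 0.555, difference +5.5 points
- w = 3: q = 0.580, difference +8.0 points
- w = 6: q = 0.646, difference +14.6 points

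The chance that 215 versus 105 women give a significant result for receivers is Φ((d − 1.96·SE₀)/SE₁), where d = q − p, SE₀ is the pooled standard error and SE₁ the unpooled one. For w = 3, with unrounded q:

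- pooled proportion = (105 × 0.500 + 215 × 0.580)/320 = 0.553
- SE₀ = √(0.553 × 0.447 × (1/105 + 1/215)) = 0.0592
- SE₁ = √(0.50 × 0.50/105 + 0.580 × 0.420/215) = 0.0593
- (0.0796 − 1.96 × 0.0592)/0.0593 ≈ −0.61, so about 27%

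The same calculation over a range of assumed rates and waits gives these artificial differences in percentage points, with the chance of falsely favouring receivers in brackets:

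| Decliners with event by 12 months | Wait 1 month | Wait 3 months | Wait 6 months |
|---|---|---|---|
| 10% | +0.8 (3.9%) | +2.3 (8.2%) | +4.6 (19.5%) |
| 30% | +2.0 (5.5%) | +6.0 (18.0%) | +11.4 (50.9%) |
| 50% | +2.8 (6.8%) | +8.0 (26.9%) | +14.6 (70.8%) |
| 80% | +2.5 (8.2%) | +6.6 (34.3%) | +11.1 (77.7%) |

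The documents give neither the wait nor the rate, and nothing in them points to a wait as long as 6 months. That column only shows how the effect grows.

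**Which comparisons are exposed.**

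- 1a(i) concerns characteristics that exist at baseline, so it is not affected.
- 2a(i) follows high-score receivers over time. 2a(ii) compares high-score with low-score receivers. 2b and 2c compare affected with unaffected receivers. All these women share one clock, so none of these is affected.
- The power statement rests on 2c at two weeks, so it is not affected.
- What remains is 1a(ii) and the receiver-versus-decliner part of Aim 2.

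**The case against.** A reader might infer that the schedule biases 1a(ii) by construction. The documents do not support that. Screening is described as a category of agreement with guidelines, which reads as a status rather than a tally since enrolment. If that status is judged on a fixed look-back, unequal calendar time creates no artificial difference under a constant rate. The wording that would settle it is in a supplementary file not shown, and an article's silence on item wording is not an error. This part of the objection stands, so the bias can only be called possible.

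The sizes are also hypothetical: the wait, the rate, its constancy and cumulative scoring are all assumed. A constant rate starting from zero at baseline may fit poorly with periodic screening in women who may already be screened. At a 1-month wait the excess is small even under cumulative scoring. This stands too.

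The two clocks also have a rationale. Decliners have no disclosure date, and hypotheses 2a and 2b need a full year after disclosure. That justifies the receivers' schedule. It does not give 1a(ii) a time point for decliners or equalise the windows in that comparison.

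Finally, Statistical analyses lists confounders only as examples, so adjusting for follow-up time is not ruled out. That would help little here: decliners sit at about 12 months and receivers above it, so the covariate barely overlaps between the groups and the adjusted effect would rest on extrapolation.

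**Conclusion.** The point holds in a limited form. Three things rest on the article's own text: the two groups are timed from different events, the 1a(ii) time point does not exist for decliners, and the single 12-month period does not fit receivers with any wait.

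Bias in favour of receivers is conditional. It arises if items count events since baseline, or events ever done such as preventive surgery, which can only accumulate. At an assumed 50% among decliners by 12 months and a constant rate, it is about +3 points for a 1-month wait and +8 points for 3 months. For events as rare as 10% it is about +1 and +2 points. With a fixed look-back the artificial difference in screening is about zero. The exposure is confined to 1a(ii) and the Aim 2 receiver-versus-decliner comparison. This is a cheap improvement worth making, not a flaw in the study's main comparisons.

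**What to change.** Choose one of two ways to put the groups on equal windows:

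1. Send decliners' final questionnaire at 12 months plus the running median of receivers' enrolment-to-disclosure wait.
2. Keep the mail-out dates, but score screening and preventive uptake in both groups only over the 12 months before the final questionnaire. For a receiver this is the year since disclosure; for a decliner, the year since enrolment.

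Then state the 1a(ii) time point for decliners to match, and correct the 12-month wording in the Abstract and under Measures so that it fits the receivers' schedule. If Additional file 1 already fixes such a look-back, saying so in the text would settle the screening part. Do not rely on months from baseline to final questionnaire as a covariate.

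Cost: the first option moves a mail-out date, so decliners' follow-up ends somewhat later, and it matches the windows on average rather than woman by woman. The second needs the timing of the last screen and of any preventive step to be recorded. Neither changes the sample size.

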**Fig. 2 Fig2:**
[figure not shown]
Study design and flow of participants through study

### Participants

#### Inclusion criteria

Approximately 400 women will be recruited to this study from the existing ViP cohort. Only women aged 18 years will be recruited. Both index cases and their affected and unaffected family members will be invited to participate in this study. Women will be eligible if they have either a low (*N* = 200) or a high PRS (*N* = 200). Each group will be stratified by disease status, such that about 100 affected and 100 unaffected women are included in each study group (Fig. 3).

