#### Statistical analyses

For each of the main outcome variables (e.g. breast cancer anxiety), linear or logistic regression will be used as appropriate. Further multivariable analyses will be used to adjust for potential confounding variables (e.g. age, parity, stressful life events). Appropriate regressions will be performed to investigate whether outcomes differ between receivers and decliners (hypothesis 1a) and between subgroups of affected and unaffected women (hypothesis 2c) and those receiving either a low or high PRS (hypothesis 2b and 2c). Repeated measurements will be analyzed using linear mixed models to assess how outcomes change over time among receivers (hypothesis 2ai and 2b). This approach adjusts for the repeated measures per person and also allows for missing values.

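### Index cases and their relatives are enrolled together, but the models named handle correlation only within a woman, so standard errors may be misstated

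*Protocol article*

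**What the plan says.** The protocol article describes the sample twice. Under Study objectives and hypotheses the 400 invited women are drawn from the ViP cohort, "including a mixture of index cases and family members". Under Inclusion criteria, "Both index cases and their affected and unaffected family members will be invited to participate in this study". The same section sets 200 women with a low and 200 with a high PRS, so that "about 100 affected and 100 unaffected women are included in each study group". Neither section limits enrolment to one woman per family.

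For single time points, the Statistical analyses section says that "linear or logistic regression will be used as appropriate". Its examples of adjustment variables are age, parity and stressful life events; family is not among them. It continues: "Appropriate regressions will be performed to investigate whether outcomes differ between receivers and decliners (hypothesis 1a) and between subgroups of affected and unaffected women". For change over time, "Repeated measurements will be analyzed using linear mixed models to assess how outcomes change over time among receivers", and the section explains what this achieves: "This approach adjusts for the repeated measures per person and also allows for missing values". No family random effect, GEE or cluster-robust standard error is named. The Sample size and power section mentions no design effect.

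**The concern.** Women from one family share a cancer history and part of the genotype that makes up the PRS. The article itself treats the decision to receive a result as partly a family matter: the response-cost items ask about the effect on the family, and the self-efficacy items ask about family opposition. Correlated uptake and correlated breast cancer anxiety between relatives are therefore plausible.

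Regression without a family term, and a mixed model whose only stated level is the woman, treat relatives as if they were unrelated. The resulting error can go either way. Where relatives tend to share the status being compared (plausible for uptake and for PRS group), the standard error is too small and the test too liberal. Where relatives tend to differ on it, the standard error is too large and the test conservative. The second case is possible for affected versus unaffected women, because the cohort description says that few relatives have had cancer. No single inflation factor corrects both, so the model has to carry the family structure.

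**Working it through.** **Inputs from the Sample size and power section.** Two-sided 5% level; IES standard deviation 14.2; difference 7 points; 80% power claimed for affected versus unaffected high-PRS receivers at 2 weeks (hypothesis 2c); 400 enrolled, 320 completing, 215 of them receivers.

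**Assumed, because the article does not give them.** Women per family in the compared sample, m = 1.25 to 3. ICC = 0.05 to 0.30. With unequal families, m is best read as Σm²/Σm, the family size seen from the average woman, which is larger than the simple mean.

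**Step 1: the plan's own figure under independence.** Needed per group: 2 × (1.960 + 0.842)² × 14.2² / 7² = 64.6, so 65. If the 215 receivers split evenly over the four PRS-by-disease cells (an assumption), each cell has 215/4 = 53.75 women. Power is then Φ(7 / (14.2 × √(2/53.75)) − 1.960) = Φ(2.556 − 1.960) = 72.4%. So 80% is not reproduced on that split even before clustering. That is a separate matter; 72.4% serves here only as the baseline.

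**Step 2: relatives fully share the compared status.** Design effect DE = 1 + (m − 1) × ICC. True two-sided error of an unadjusted nominal 5% test = 2 × [1 − Φ(1.960/√DE)]. The number needed is 65 × DE, and power uses 53.75/DE per group.

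| m | ICC | DE | True type I error | Needed per group | Power at 53.75 per group |
|---|---|---|---|---|---|
| 1.25 | 0.05 | 1.01 | 5.1% | 66 | 71.9% |
| 2 | 0.10 | 1.10 | 6.2% | 72 | 68.3% |
| 2 | 0.20 | 1.20 | 7.4% | 78 | 64.5% |
| 2 | 0.30 | 1.30 | 8.6% | 85 | 61.1% |
| 3 | 0.30 | 1.60 | 12.1% | 104 | 52.4% |

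**Step 3: the compared women form fully discordant pairs.** With one woman of each pair in each group, the variance of the difference is multiplied by (1 − ICC), and the unadjusted test ignores this. True error = 2 × [1 − Φ(1.960/√(1 − ICC))]. For ICC 0.05, 0.10, 0.20 and 0.30 this is 4.4%, 3.9%, 2.8% and 1.9%. If the pairing were modelled, power at 53.75 per group would be 74.6%, 76.8%, 81.5% and 86.3%, against 72.4% when every woman is unrelated.

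**Step 4: which case applies.** Steps 2 and 3 are the two extremes. A real family can contain women who agree on PRS group and differ on disease status, or the reverse, so each contrast in this study probably lies between them.

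**The case against.** The strongest reply is that this is a short analysis section in a journal article, and that random-effect levels and robust errors are commonly left to a fuller plan. The wording about appropriate regressions leaves room for a family term, and the remark on repeated measures could be praise of mixed models, not a full list of levels. A reader might infer that every model assumes independent women. The article does not say that; it is an inference from the methods named. What remains is that the section does state which correlation is handled, and it leaves out the one that its own recruitment creates.

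The second reply is that several women per family may be uncommon. About 400 women come from some 3700 with genotypes, or 10.8%. If selection were random and each family had two genotyped members, an enrolled woman would have 0.108 enrolled relatives on average. For ICC 0.1 to 0.3 the design effect would then be 1.011 to 1.032 and the true error 5.1% to 5.4%. With three genotyped members and ICC 0.3 it would be 1 + 0.216 × 0.3 = 1.065 and about 5.8%. Intermediate-PRS women are also ineligible, which removes some relatives, although similar scores within a family work the other way. Further, the cohort description implies that the roughly 200 affected women are mostly index cases and so largely from different families. With near 200 families or more among 400 women, a simple mean above about 2 per family is hard to reach. This reply stands as to size: 12.1% is an upper bound, and a near-null effect is plausible.

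The third reply is that the conservative case for hypothesis 2c needs many pairs in which both women have a high PRS, both receive it, both answer at 2 weeks, and only one is affected. Nothing in the article shows that such pairs are common. This also stands.

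**Conclusion.** The mismatch is real. Related women are enrolled by design without a one-per-family rule, and no stated model accounts for family, so standard errors and p-values may be misstated wherever several relatives are analysed. A reader might go further and conclude that the errors and p-values are wrong for uptake, PRS group and disease status alike. The documents do not support that, because they give no number of families, no family size and no ICC.

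Under the assumed ranges the true error of a nominal 5% test runs from about 5.1% to 12.1% when relatives fully share the compared status, and from 4.4% to 1.9% when they are fully discordant. Both size and direction are conditional on family structure. The point is worth correcting because the remedy is nearly free, but it does not undermine the study.

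**What to change.** In the Statistical analyses section:

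- Add a family random intercept to the linear mixed models, with visits nested in woman and woman nested in family.
- For the linear and logistic regressions (hypotheses 1a, 2a(ii) and 2c), use GEE or standard errors clustered on family.
- Take family membership from the ViP cohort. The article describes index cases and their relatives there, so the identifier is presumably held, but this is not stated.
- Report the number of families and of women per family, so that readers can judge how much this matters.

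The cost is analysis wording only; recruitment and questionnaires do not change. Intervals become slightly wider where relatives share the compared status and may narrow where they differ. If clustering proves negligible, the results will hardly move.
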